## Abstract

**Background:**

Food addiction is one of the behavioral factors that play an important role in the pathogenesis of obesity. Much evidence is available suggesting intestinal microbiomes can play a role in eating behavior, body composition, and BDNF levels, and they can be modified by time-restricted feeding (TRF). So, this study will aim to evaluate the effect of TRF on anthropometric measures, eating behavior, stress, and serum BDNF and LBP levels in women with overweight/obesity and food addiction.

**Methods:**

We will carry out a randomized clinical trial for 8 weeks to evaluate the effect of a TRF on anthropometric measures, eating behavior, stress level, serum BDNF and LBP levels in women with overweight/obesity and food addiction.

**Discussion:**

Given the effect of BDNF on regulating eating behavior and body weight and the effect of dietary restrictions on BDNF and the gut microbiome, the TRF diet could possibly be a new way to successfully manage weight through modifying BDNF in people with eating disorders, including food addiction.

**Trial registration:**

Iranian Registry of Clinical Trials IRCT20131228015968N7. Registered on 25 October 2020.

**Supplementary Information:**

The online version contains supplementary material available at 10.1186/s13063-022-06439-x.

## Background

Despite recent advances in our understanding of the physiological mechanisms that regulate body weight, obesity remains a major health problem worldwide with multiple consequences, including metabolic and endocrine complications, malignancy diseases, and psychosocial problems [1]. The global obesity epidemic suggests that obesity is not only triggered by a lack of motivation for weight loss, loss of control over food intake, and continued excessive consumption despite knowing negative consequences may also develop in many individuals [2]. The term of “food addiction” is used to describe these compulsive feeding behaviors associated with loss of control of eating [3, 4] with a prevalence rate ranging from 19 to 56.8% in different populations [4, 5]. The prevalence of food addiction among Iranian women with obesity was 26.2% based on the Iranian version of the Yale Food Addiction Scale [5]. Feeding behavior can be managed by both homeostatic (associated with energy demands/stores) and hedonic pathways (brain dopaminergic reward system) which controls energy intake and body weight [6]. So, understanding the mechanisms underlying feeding behavior might be helpful in finding the way of being more efficient in obesity management. Some appetite-regulating hormones such as brain-derived neurotropic factor (BDNF) have been shown to play a modulatory role in reward-related behaviors through both aforementioned pathways [7, 8]. So, it seems that modification in eating behavior through modulation of these hormones may play a key role in some cases of weight gain and obesity such as food addicted ones. Peripheral and central levels of BDNF are associated and BDNF can cross the blood-brain barrier in both directions [9]. Gut microbiota modulation is one of the new therapeutic approaches for managing feeding behavior [10]. Based on previous studies, gut microbiota may play an important role in regulating obesity, energy balance, and also the host eating behavior through affecting appetite and hormone levels such as BDNF [10, 11]. BDNF is a neuromodulator playing an important role in the homeostatic control of food intake and energy expenditure regulation [8]. The regulatory role of BDNF in hedonic feeding has also documented through the mesolimbic reward pathways [8] including consumption of palatable food. So it is not surprising that disruptions in these aforementioned regulatory roles of BDNF lead to hyperphagic behavior and obesity [12]. So far, it seems that gut microbiota improvement might have a modulatory effect on central levels of BDNF [13–16].

Several methods have been suggested to modify and improve the gut microbiota such as probiotic and prebiotic supplementation and fasting [17, 18]. Time-restricted feeding (TRF) is a kind of fasting recommending individuals to confine the eating window to a specified number of hours per day, without altering calorie intake or diet quality [19]. TRF could alter the diversity or abundance of the gut microbiome in response to the body’s circadian rhythm [20]. In turn, gut microbiota can modulate BDNF expression in the brain [21] and also feeding behavior [10]. Feeding behavior can be affected by stress level in individuals and a significant correlation between food addiction and stress has been reported in individuals with overweight and obesity [22, 23]. Lipopolysaccharide (LPS) is an endotoxin produced by altered gut microbiota and is associated with low-grade inflammation in obesity [24, 25]. Lipopolysaccharide-binding protein (LBP) is an acute phase protein produced by the liver which binds to LPS and is a part of LPS-induced inflammation. Serum LBP can be measured to evaluate changes in the gut microbiome [24, 25]. On the other hand, previous clinical trials documented that TRF might have a favorable effect on weight loss, reduction of insulin resistance, systolic blood pressure, and fasting glucose levels [26]. However, some previous studies did not show any advantages of using TRF on body weight management [27, 28]. Therefore, these aforementioned discrepancies may be explainable by ignoring the role of feeding behavior disorders such as food addiction on body weight management. Hence, the aim of this clinical trial is to investigate the effect of TRF on anthropometric indices, stress level, eating behavior, and serum levels of BDNF and LBP in women with overweight/obesity and food addiction.

### Objectives and hypothesis

Primary aims of this clinical trial are the changes in anthropometric indices (including weight, BMI, hip circumference, waist-to-hip ratio, fat mass, muscle mass) and food addiction score. Secondary aims are changes in stress level, eating behavior, and serum levels of BDNF and LBP. A TRF is expected to improve these aforementioned indicators.

## Methods and design

### Study design

We will carry out an 8-week double-blind randomized controlled trial. The flow chart of the study is presented in Fig. 1. This intervention will be conducted in the nutrition clinic of Shahid Beheshti University of Medical Sciences in Tehran, Iran, to evaluate the effect of TRF on anthropometric indices, eating behavior, stress, serum BDNF and LBP levels in women with overweight/obesity, and food addiction (Fig. 2).

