### Study population

Women with overweight or obesity (BMI: 26– 39.9 kg/m^2^) and with food addiction will be recruited from nutrition clinic of Shahid Beheshti University of Medical Sciences (SBMU) through advertisement and face-to-face communication. The diagnosis of food addiction will be based on the YALE Food Addiction Scale [29]. Women with overweight or obesity that obtain the necessary score will be enrolled in the study. Subjects who meet the inclusion criteria will be completely informed about the protocol of the study. Each participant will sign the informed consent form.

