### Inclusion and exclusion criteria

For the present study, 60 adult women with the following inclusion criteria will be included: aged 20–65 years; BMI: 26–39.9 kg/m^2^; willingness to participate in the study; confirmation of food addiction after obtaining the necessary score (at least 1 clinical score+ at least having 3 out of 7 criteria) from the YALE food addiction questionnaire; not having any diseases such as cancer, diabetes, newly hypothyroidism, renal or liver failure; non-pregnant or lactating; not perimenopause (women with irregular menstruation due to menopause or less than 2 years after amenorrhea); not participating in a weight loss diet during the last 2 months; and were not smokers.

Patients will be excluded if taking any antibiotics in the last 1 month or during the study; taking any medication affecting study outcomes regularly; using probiotic products (probiotic supplements, yogurt, cheese, cakes, biscuits, and probiotic pasta) continuously (more than once a week) in the last month or during the study; using weight-loss or appetite-suppressing medications; drinking alcohol at any levels before or during the study; and women with irregular menstruations. Also, we will exclude participants who refuse to continue the study, need antibiotics or have difficulties in fasting for 14 h a day in the intervention group.

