### Randomization, sequence generation, and concealment

Participants will be randomly allocated into two groups: the group receiving a low-calorie diet with the time-restricted feeding protocol or the control group receiving a low-calorie diet and will be followed up for 8 weeks. Stratified blocked randomization method is used to randomly assign people to two groups. The sequencing will be generated by one of the authors (AS) who is not going to assign participants into the study, so, allocation concealment will be ensured, as the author will not release the randomization code until the patient has been recruited into the trial by other authors (HI and [name]), which takes place after all baseline measurements have been completed. Participants are classified into overweight (26–29.9 kg/m^2^), grade 1 (30–34.9 kg/m^2^), and grade 2 obesity (35–39.9 kg/m^2^) based on BMI and randomly assigned to one of the control or TRF groups. Separate randomization is performed within each group for each BMI class. The size of the blocks is 4, two allocations are given to TRF group (A) and two allocations to Control Group (B). Six different permutations of AABB, ABAB, BBAA, BABA, ABBA, and BAAB will be created.

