### Intervention

In this study, patients receive the relevant diets for 8 weeks based on the group they are placed in. In both groups, after calculating the amount of calories required by each individual using the Mifflin formula [30] as much as 300–500 kcal will be deducted from the total energy required for each person (a 500 kcal reduction from calories is using for most of the cases, except for whom the calorie falls below 1200 kcal/d with 500 kcal reduction. In these cases, 300–400 kcal reduction will be used.) and accordingly, the low-calorie diet plan is given to each individual. The diet in each group will consist of 50–55% carbohydrates, 15–20% protein, and 30% fat. Patients in the TRF group will receive their meals from 10 h a day from 10 am to 8 pm [31] while the control group will have less than 12 h fasting.

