### Adherence

In order to control the participants in terms of adherence to the regimen and prevent the loss of samples, they will be followed up twice a week by phone call. At every phone call we will make sure if the cases are still in the study and they do not have exclusion criteria (any need for antibiotic consumption, consuming probiotics, and…). Also, a 24-h recall of the last day is obtaining from individuals and it is compared to their diet to make sure if they are adhering to the diet. The data of the patients with more than 90% compliance with the intervention will be analyzed.

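### The trial is labelled double-blind, but women carry out the meal timing themselves and cannot be blind, so the questionnaire outcomes lack the protection the label implies

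*Protocol article*

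**What the plan says.** The Study design section of the protocol article makes an affirmative claim: "We will carry out an 8-week double-blind randomized controlled trial". It does not say which parties are blinded. The abstract's Methods paragraph and the caption of Fig. 1 describe a randomised trial without mentioning blinding.

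The Intervention section gives both arms a calorie-reduced diet built by the same rules, with the same macronutrient ranges. The arms are separated by timing. For the intervention arm: "Patients in the TRF group will receive their meals from 10 h a day from 10 am to 8 pm". For the comparator: "the control group will have less than 12 h fasting". The Inclusion and exclusion criteria add a reason for exclusion that concerns one arm only, namely women who "have difficulties in fasting for 14 h a day in the intervention group".

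The Randomization section describes one related safeguard: "the author will not release the randomization code until the patient has been recruited into the trial".

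The Study outcomes section names six anthropometric indices and the food addiction score as primary. Stress, eating behaviour, serum BDNF and serum LBP are secondary.

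**The concern.** A blinding label tells readers which biases have been dealt with. When the participant supplies the measurement by answering a questionnaire, the protection that matters is that she does not know her arm. Here the treatment is something she does every day by the clock, so that protection cannot exist, yet the article claims a design that would normally include it.

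The outcomes at stake are the food addiction score, which is primary, and the stress and eating behaviour scores, which are secondary. The Objectives and hypothesis section states that time-restricted feeding is expected to improve all the indicators. Women who know that they were given the restricted window may report better control of eating for that reason alone. A reader who trusts the label would not discount a difference in these scores for expectation, and should.

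**Working it through.** The documents give no figure for blinding, so the check sets the sections side by side.

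1. **What separates the arms (Intervention).** The window runs from 10:00 to 20:00, so eating time is 20 − 10 = 10 h and fasting time is 24 − 10 = 14 h. This agrees with the 14 h fast named in the exclusion criteria. The control arm fasts for less than 12 h. The two regimens therefore do not overlap: they differ by more than 14 − 12 = 2 h of fasting per day. Calorie and macronutrient rules are the same in both arms, and no sham window is described.

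2. **Who carries out the contrast.** The woman does, at every meal. She cannot follow a 10 am to 8 pm window without knowing that she has been given one.

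3. **The arm-specific exclusion (Inclusion and exclusion criteria).** A rule about difficulty with the 14 h fast, confined to the intervention arm, can operate only if the woman knows that she is meant to fast that long and whoever applies the rule knows her arm. This is the clearest support outside the Intervention section.

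4. **What the randomisation safeguard covers (Randomization).** Withholding the code until the patient has been recruited is allocation concealment. It prevents selective enrolment and ends at assignment. It is not blinding during follow-up.

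5. **Which outcomes depend on the participant's own answers (Study outcomes and the measurement text that follows).**
   - Primary: weight, BMI, hip circumference, waist-to-hip ratio, fat mass and muscle mass make six measured indices. The food addiction score makes 6 + 1 = 7. One of seven is participant-reported.
   - Secondary: stress (PSS-14) and eating behaviour (an 18-item three-factor questionnaire) are participant-reported. BDNF and LBP are assayed by ELISA. Two of four are participant-reported.
   - Together, 1 + 2 = 3 of the 7 + 4 = 11 named outcomes are fully exposed.

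   The Yale questionnaire is named for diagnosis at entry and is not restated for follow-up. That the food addiction score comes from it is an assumption, but the article names no other source.

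6. **Result.** The label in Study design conflicts with the regimens in Intervention and with the arm-specific exclusion. The conflict holds for participants, and so for the three outcomes that they report.

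**The case against.** **The label may mean masked assessors and a masked analyst.** The article does not say so. Even if it did, the participant is the assessor for the three questionnaire outcomes, so masking other people would not protect them.

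**An article condenses a fuller protocol.** This stands, and it limits the point. A reader might infer that nobody in this trial is masked. The documents do not support that: silence in a condensed article does not show that those who weigh, measure, assay or analyse are unmasked. Brevity excuses leaving out who is masked, but it does not excuse a stated property that the described treatment rules out.

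**Some of the apparent evidence is weak.** This also stands. The Study population section says: "Subjects who meet the inclusion criteria will be completely informed about the protocol of the study". That is information given before consent and does not show that a woman learns her allocation, although it leaves no support for the idea that women are kept unaware of what is being compared. The Adherence section says of participants that "they will be followed up twice a week by phone call" and that "a 24-h recall of the last day is obtaining from individuals and it is compared to their diet". A reader might infer that the callers must know the arm. Because both arms share the same calorie and macronutrient rules, checking a recall against a diet plan does not prove it. The conclusion rests on the Intervention section and the arm-specific exclusion.

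**The effect may be modest.** Both arms receive an active diet, and the calls are described without distinction by arm. That reduces differential expectation but does not remove it, because the thing being tested is still visible to the woman.

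**Lack of participant blinding is unavoidable here.** Agreed. With self-administered meal timing, open participants are not a design fault. The fault is the claim.

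**Conclusion.** The point holds for participants. The trial cannot be double-blind in any sense that covers them, and the primary food addiction score and the secondary stress and eating behaviour scores lack the protection claimed. That is three of the eleven named outcomes, one of them primary. The direction of concern is towards the expected benefit of time-restricted feeding, but the size of any bias cannot be derived from the documents. The conclusion assumes that the food addiction score is questionnaire-based at follow-up as it is at entry.

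Two further inferences would go too far. A reader might infer that the main conclusion should therefore rest on measured weight. Weight is the basis of the sample size, but making it the sole basis for the conclusion would re-rank the listed primary outcomes, and a wrong blinding label does not settle that question. A reader might also infer that the trial registration repeats the label. The article gives only the registration number and date, so what the record says is unknown.

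The correction leaves the randomisation, the sample size and the planned tests untouched. It does change what the trial may claim for its questionnaire results, so it should be made.

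**What to change.** - In Study design, remove the term double-blind and describe participants as unblinded.
- Name only those parties who are actually masked. Recruitment began in November 2021, so confirm what has been done in practice before writing that assessors, laboratory staff or the analyst are masked.
- Where not already done, run the BDNF and LBP assays on coded samples, and analyse with the arms under neutral two-letter codes until the primary analysis is locked. The Randomization section already identifies A as the TRF group and B as control, so those letters would mask nothing unless they are reassigned. Use a fresh assignment or other labels.
- State that the food addiction, stress and eating behaviour scores are unblinded, and that differences in them will be interpreted with that caution.

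Cost: a less favourable design label, minor coding work, and whatever step the Protocol amendments section requires for a change to the design description.

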**Fig. 1 Fig1:**
[figure not shown]
Protocol flow diagram; we will carry out an 8-week randomized controlled trial to determine the effects of a time-restricted feeding on anthropometric indices, body composition, eating behavior, stress, and brain-derived neurotrophic factor (BDNF) and lipopolysaccharide-binding protein (LBP) levels in overweight and obese women with food addiction

**Fig. 2 Fig2:**
[figure not shown]
Timeline of the study; we expect the duration of the trial will be 24 months

The protocol is written in line with the Standard Protocol Items: Recommendations for Interventional Trials (SPIRIT) checklist (Additional file 1).

### Sample size

The number of participants was calculated based on the changes in body weight, as a primary outcome. The number of participants in this study was determined by the difference in weight loss between the TRF and control groups of 2.3 kg [28]. This difference has a probability of 95% (*α*=0.05) and a power of 80% (*β*=20%), which is statistically significant. Using this method, each group was estimated to have 26 participants, so that after taking into consideration 20% attrition, every group will be comprised of 30 participants. Collectively, 60 women with overweight or obesity and food addiction will be enrolled.

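### Thirty per arm does not cover 20% attrition on 26 per arm: 24 remain, and power is about 77%, not the stated 80%

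*Protocol article*

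**What the plan says.** The Sample size section sizes the trial on one outcome: "The number of participants was calculated based on the changes in body weight, as a primary outcome". The target is a "difference in weight loss between the TRF and control groups of 2.3 kg", with α = 0.05 and 80% power. From this, "each group was estimated to have 26 participants, so that after taking into consideration 20% attrition, every group will be comprised of 30 participants". The total follows: "Collectively, 60 women with overweight or obesity and food addiction will be enrolled". The Inclusion and exclusion criteria section repeats the figure of 60.

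Allocation is 1:1 in blocks of four (Randomization section), and the between-group comparison is a t test (Statistical analysis section). The Adherence section limits the analysed data to participants with more than 90% compliance. The article gives no standard deviation for weight change and no other attrition rate.

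**The concern.** One sentence gives three numbers: 26 needed, 20% lost, 30 enrolled. Any two of them fix the third, and these three do not agree. The attrition allowance is there so that the number needed for 80% power is still available after the expected losses. If the inflation is wrong, the trial misses its stated power when dropout goes exactly as planned.

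The allowance is also the only protection given to the analysed number, and other parts of the protocol may draw on it. The Inclusion and exclusion criteria section removes women during the study for several reasons, and the Adherence section filters on compliance. The article does not say whether the 20% is meant to cover these losses.

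**Working it through.** **Inputs.** From Sample size: difference 2.3 kg, α = 0.05, power 80%, 26 per arm needed, 20% attrition, 30 per arm (60 in total) enrolled. From Statistical analysis: two-sample t test. My assumptions: a two-sided test, and an SD back-solved from the protocol's own claim that 26 per arm gives 80% power.

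**1. Can 30 be reproduced?**
- Standard inflation, n/(1 − d): 26/0.80 = 32.5, so 33 per arm and 66 in total.
- Cruder inflation, n × (1 + d): 26 × 1.20 = 31.2, so 32 per arm and 64 in total.
- Neither gives 30, and rounding does not bridge the gap.
- The rates that would give 30 are 1 − 26/30 = 13.3% (standard) and 30/26 − 1 = 15.4% (cruder). Neither is 20%.

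**2. What 30 per arm leaves.** 30 × 0.80 = 24 per arm, two short of 26. With 33 per arm, 33 × 0.80 = 26.4, which meets the requirement.

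**3. Implied SD.** In the normal approximation, SD = 2.3 × √(26/2)/(1.960 + 0.842) = 2.96 kg. With the noncentral t distribution it is 2.90 kg, a standardised difference of 2.3/2.90 = 0.79. The figure 26 could also be the result of rounding up. In the limit where 25 per arm gives exactly 80%, the SD is 2.90 kg (normal) or 2.84 kg (t).

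**4. Power with 24 per arm.** In the normal approximation the SD cancels once power is anchored, because the standardised effect scales with √n:
- Anchored at 26: 2.802 × √(24/26) = 2.692; 2.692 − 1.960 = 0.732; Φ(0.732) = 76.8%.
- Anchored at 25 (rounding limit): 2.802 × √(24/25) = 2.745; 2.745 − 1.960 = 0.785; Φ(0.785) = 78.4%.

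| Per arm | t test, 26 gives exactly 80% (SD 2.90 kg) | t test, 25 gives exactly 80% (SD 2.84 kg) |
|---|---|---|
| 24 | 76.6% | 78.3% |
| 25 | 78.4% | 80.0% |
| 26 | 80.0% | 81.6% |
| 30 | 85.5% | 86.9% |
| 33 | 88.7% | 89.9% |

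With a one-sided test anchored at 26 (normal approximation), power at 24 is 77.2%. At the rounding limit, 2.486 × √(24/25) − 1.645 = 0.791, so about 78.6%.

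No variant reaches 80%. This follows from the protocol's own statement: if 24 or 25 per arm were enough, 26 would not be the number required.

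**5. Detectable difference at 80% power with 24 per arm.** Anchored at 26, it is about 0.826 × 2.90 = 2.40 kg. At the rounding limit it is about 2.3 × √(25/24) = 2.35 kg.

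**6. If the compliance filter removes women beyond the 20%.** The protocol gives no figure for this, so these are illustrations only. On the same anchor (SD 2.90 kg), 20 per arm gives 68.5% and 18 per arm gives 63.7%.

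**The case against.** The arithmetic cannot be defended, but its weight can be questioned. The shortfall is two analysed women per arm, about 2 to 3 points of power, and it does not change the design or the hypothesis. It arises only if attrition really reaches 20%. At 13.3% or less the target is met, and with no loss 30 per arm give about 85%. That is fair, and the claim should be read as conditional on the stated attrition. But 20% is the rate the protocol itself chose to plan for.

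A second objection is that 77% rests on an unstated SD. The power at 24 per arm depends on how 26 was reached and on the sidedness of the test, so a range is needed. It runs from 76.6% to 78.4% two-sided, and every value is below 80%. A journal article may leave the SD to the full protocol, so its absence is not counted here as an error.

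Third, the figures for 20 and 18 per arm rest on retention numbers that appear nowhere in the protocol, and the 20% may already include the non-compliant. That also stands. Those figures show sensitivity and do not carry the conclusion.

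**Conclusion.** The point holds. The stated requirement, attrition allowance and enrolment number contradict each other, and nothing elsewhere in the article corrects them. At the stated 20% attrition, 24 per arm remain. Taking 26 per arm as the number needed for 80% power, the t test then has 76.6% power for 2.3 kg, or up to 78.3% if 26 was rounded up. The inflation error depends on no assumption. The size of the power loss rests on that anchor and, for these two figures, on a two-sided test. The loss is modest, but it falls on the figure that justifies the trial's size, and it would grow if compliance exclusions come on top of the 20%.

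**What to change.** Correct the Sample size statement. Any one of these makes it consistent:

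- Keep 60 women and say that 30 per arm allows for attrition of up to 13% at 80% power.
- Keep 60 women and say that, with 20% attrition (24 per arm), power for 2.3 kg is about 77%.
- Keep both the 80% power and the 20% allowance, and enrol 33 per arm, 66 in total.

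The first two cost one sentence and a slightly less favourable stated allowance or power. The third costs six more women. It is still open, because the Trial status section puts the trial in its enrolment stage, but the Protocol amendments section requires a formal amendment for a change of sample size.

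In the same sentence, give the SD used (about 2.9 kg is implied) so that 26 can be reproduced, and say whether the attrition figure includes women left out for non-compliance.
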